##### Peak Expiratory Flow Measurement

Recorded statistics for peak expiratory flow at each time point will be calculated for each group, and changes over time will be illustrated. Furthermore, the least mean square and 95% confidence interval at each assessment time point, as well as the least mean square difference and 95% confidence interval, will be calculated. The amount of change from day 1 will be used as the result variable by using MMRMs, and intergroup comparisons will be conducted.

##### Comprehensive Assessments by Physicians

The number and percentage of research participants at the 3 comprehensive assessment levels will be calculated for days 8 and 15, and intergroup comparisons will be conducted using the Fisher exact test.

#### Safety Analysis

The safety endpoints include adverse event incidence and rates. The 95% confidence intervals for determining binomial distribution accuracy will be calculated for the estimated rates that relate to the incidence number and presence of adverse events. Intergroup comparisons will be conducted using the Pearson Chi-squared test or Fisher exact test. The significance level of hypothesis testing will be set at 5% for both sides.

Recorded metrics that are calculated for continuous data, such as clinical inspection criteria and vital signs, and suitable methods (eg, number and percentage) will be used as categorical variables for each group.

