**Conclusions:**

The RACCO (Randomized Ciclesonid COVID-19) study will provide definitive comparative effectiveness data and important clinical outcomes data between the ciclesonide and symptomatic treatment groups. If the hypotheses that pneumonia exacerbation rate reduction is more significant in the ciclesonide treatment group than in the symptomatic treatment group and that ciclesonide is safe for use are valid, ciclesonide will serve as an important therapeutic option for patients with COVID-19.

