### Objectives

The primary objective of the RACCO (Randomized Ciclesonide COVID-19) trial is to compare the pneumonia exacerbation rate between the ciclesonide and symptomatic treatment groups, which consist of patients with COVID-19, and to determine the efficacy of ciclesonide. The secondary objective is to investigate the safety of ciclesonide administration by comparing the rate of adverse events between both groups. In addition, changes in clinical and laboratory findings and changes in the number of copies of the viral genome over time will be monitored between the 2 treatment groups.

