### Statistical Methods

#### Sample Size

The sample size for the RACCO trial will be 90 patients (ie, n=45 for the ciclesonide group and n=45 patients for the symptomatic treatment group) to control for pneumonia onset and allow for the full analysis of study participants to complete the study.

Based on our experience, 35% of patients who have tested positive for COVID-19 without pneumonia symptoms will have pneumonia during the follow-up period. The necessary number of cases for a 2-sided α-level of 10% and power of 80% for cases with incidence percentages of 30%, 35%, 40%, and 50% in the standard treatment group and incidence percentages of 5%, 10%, 15%, and 20% in the trial treatment group are shown in Figure 3.

The effect of controlling the pneumonia onset percentage to 25% would mean that the drug is clinically effective. The numbers highlighted in grey in Figure 3 are the sample sizes necessary for detecting effects with a power of 80% in cases where a 25% pneumonia onset control is present. For example, if the pneumonia onset percentage of the standard treatment and trial treatment groups were hypothetically set to 35% and 10%, respectively, the required sample size would be 84. Factoring in cases where consent may be withdrawn during the trial or participants drop out, the target number of cases for the present research will be set at N=90. The target number of cases will be specified for each implementing medical institution.

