#### Analysis Sets

This study will contain the following 3 analysis sets: the full analysis set, the per protocol set, and the safety analysis set. The full analysis set has been defined as research participants who have been registered in the proposed research, have been randomized, have had their baseline CT image data acquired, and have no serious protocol violations.

The per protocol set has been defined as research participants from the full analysis set after removing cases with the following serious protocol violations: selection criteria violations, exclusion criteria violations, prohibited drug violations, prohibited treatment violations, and a medicine administration compliance of below 90%.

In the safety analysis set, all participants will be analyzed.

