Other trials that involve ciclesonide are in progress or in planning. Covis Pharma has launched a phase III clinical trial in the United States to evaluate the asthma drug, ciclesonide (ALVESCO), in treating nonhospitalized patients with symptomatic COVID-19 aged ≥12 years. In this US trial, participants will be given 320 µg of ciclesonide (ALVESCO) via metered-dose inhaler twice daily, along with standard supportive care or a placebo and standard supportive care. The primary endpoint of the Covis Pharma trial is the percentage of patients who were admitted to a hospital or died by day 30 [16]. The accumulation of findings from the RACCO study together with those from the other trials will be significant in developing interventions and treatments for COVID-19.

In conclusion, the RACCO study is an ongoing open-label randomized controlled trial that will provide the most definitive comparative effectiveness data to date and other important clinical outcomes data from the ciclesonide and symptomatic treatment groups. If the hypotheses that pneumonia exacerbation rate reduction is more significant in the ciclesonide treatment group than in the symptomatic treatment group and that ciclesonide is safe for use are valid, ciclesonide will provide an important therapeutic option for patients with COVID-19 that can be rapidly implemented in clinical practice.

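### The article treats ciclesonide's safety as a hypothesis to be validated, but its only stated between-arm adverse event analysis is a test of difference, which at 45 per arm cannot show safety

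*Protocol article*

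**What the plan says.** Four parts of the protocol article bear on this.

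- **Objectives.** "The secondary objective is to investigate the safety of ciclesonide administration by comparing the rate of adverse events between both groups".
- **Safety Analysis.** On intervals: "The 95% confidence intervals for determining binomial distribution accuracy will be calculated for the estimated rates that relate to the incidence number and presence of" (the sentence closes by naming adverse events). For the comparison between arms: "Intergroup comparisons will be conducted using the Pearson Chi-squared test or Fisher exact test", with the level given as "The significance level of hypothesis testing will be set at 5% for both sides".
- **Sample Size and Analysis Sets.** The arms are "n=45 for the ciclesonide group and n=45 patients for the symptomatic treatment group". The calculation rests on pneumonia incidence alone. For safety, "In the safety analysis set, all participants will be analyzed".
- **Abstract (Conclusions) and the last paragraph of the Discussion.** Each pairs an efficacy hypothesis with a safety one. The Abstract reads "that ciclesonide is safe for use are valid, ciclesonide will serve as an important therapeutic option for patients with COVID-19", and the Discussion reads "that ciclesonide is safe for use are valid, ciclesonide will provide an important therapeutic option for patients with COVID-19".

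By contrast, Primary Endpoint Analysis plans a risk ratio and 90% and 95% confidence intervals alongside its Fisher test.

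**The concern.** A test of no difference can detect harm. It cannot establish that harm is absent or small. If safety is to be judged a valid hypothesis and the only between-arm result is a p value, the one test result that fits that judgement is non-significance. A small trial produces non-significance readily, even when the drug does raise the adverse event rate.

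The per-arm intervals do not fill the gap, because two separate rate intervals do not directly say how large an excess on ciclesonide is still compatible with the data. At stake is half of the trial's stated conclusion, about a drug given to patients with asymptomatic or mild disease.

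**Working it through.** **Inputs.** From the document: 45 per arm (Sample Size); Fisher exact or Pearson chi-squared at two-sided 5% (Safety Analysis). The document gives no background adverse event rate, so the rates below are assumptions.

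**1. The plan's own figure.** For 35% v 10%, two-sided alpha 10% and power 80%, with mean rate 0.225:

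n0 = [1.645·√(2·0.225·0.775) + 0.842·√(0.35·0.65 + 0.10·0.90)]² / 0.25² = 33.4 per arm.

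With continuity correction, n = (n0/4)·[1 + √(1 + 4/(n0·0.25))]² = 41.05, rounded up to 42 per arm. The total is 84, which matches the stated number (90 after allowance for dropout). The sizing is thus reproduced, and it concerns pneumonia only.

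**2. Chance of missing a real excess of adverse events.** All 46 × 46 possible outcome pairs at 45 per arm were enumerated:

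miss rate = 1 − Σ Bin(a; 45, p_control)·Bin(b; 45, p_ciclesonide), summed over pairs with p ≤ 0.05.

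| Control → ciclesonide (assumed) | Fisher miss | Pearson miss (uncorrected) |
|---|---|---|
| 5% → 10% (doubling) | 94% | 84% |
| 10% → 20% (doubling) | 82% | 72% |
| 15% → 30% (doubling) | 70% | 58% |
| 20% → 40% (doubling) | 54% | 44% |
| 30% → 60% (doubling) | 24% | 18% |
| 20% → 35% (+15 points) | 73% | 63% |
| 30% → 45% (+15 points) | 75% | 69% |
| 40% → 55% (+15 points) | 78% | 72% |

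By the normal approximation without continuity correction, 80% power for a doubling needs about 435 per arm at a 5% background, 199 at 10%, 82 at 20% and 42 at 30%. So 45 per arm is roughly enough for a doubling only when the background is near 30%.

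**3. What a between-arm interval would show.** The Newcombe 95% interval for p1 − p2 has upper limit (p1 − p2) + √[(u1 − p1)² + (p2 − l2)²], where l and u are the Wilson limits of each rate.

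- 5/45 v 5/45: Wilson limits 0.048 and 0.235. Upper limit = √[(0.235 − 0.111)² + (0.111 − 0.048)²] = 0.139, so the interval is −13.9 to +13.9 points.
- 9/45 v 9/45: Wilson limits 0.109 and 0.338. Upper limit = √[(0.338 − 0.200)² + (0.200 − 0.109)²] = 0.166, so the interval is −16.6 to +16.6 points.
- 9/45 on ciclesonide v 5/45 on symptomatic treatment: difference 8.9 points, Fisher p = 0.38, interval −6.5 to +24.1 points.

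The last example makes the point. The test reports no significant difference, while the data remain compatible with an excess of 24 points.

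**The case against.** **The miss rate depends on a background rate that nobody has stated.** This stands. A figure of about 80% for a doubling fits Fisher at an assumed 10% background and is not a property of the plan. Adverse Event Reporting counts abnormal laboratory and physiological values as adverse events, so the any-event rate could be well above 10%. Near 30%, a doubling would usually be detected. A higher background does not rescue the test for smaller excesses, though: 15 points is still missed about 63% to 78% of the time at 20% to 40%.

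**Safety does not rest on one p value.** This also stands. The article plans 95% intervals for the adverse event rates and summaries of laboratory values and vital signs. It plans between-arm differences with intervals for vital signs, inspection findings and peak flow, records severity and causality, and has a safety monitoring board. None of these is an interval for the between-arm difference in adverse event rates, which is the comparison that Objectives names for safety.

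**The missing interval may be in the analysis plan, or be covered by the general statement on 95% intervals under Secondary Endpoint Analysis.** Either is possible. But Safety Analysis has its own text, which names the intervals, tests and level. An interval held elsewhere would also leave the wording of the two conclusions as it is.

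**The trial is exploratory and safety is a secondary objective.** For that reason no safety margin and no sizing for harm is owed. The label does not help the conclusions, since exploratory data make it harder to call safety a validated hypothesis.

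**Conclusion.** The point holds as a mismatch between a stated conclusion and the analysis stated to support it. The article lets safety be found valid, yet the only between-arm adverse event analysis on the page is a test of difference, and at 45 per arm a non-significant result says little. The size depends on the assumed background rate. For a doubling, the miss rate runs from 94% at 5% to 24% at 30% under Fisher, and from 84% to 18% under Pearson.

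A reader might infer that the plan will declare ciclesonide safe whenever the test is non-significant. The documents do not say that. The phrase appears in conditional closing sentences, and Objectives speaks only of investigating safety. A reader might also infer that the trial is defective for lacking a margin or adequate power for harm. An exploratory trial needs neither. What remains is a worthwhile and inexpensive improvement that changes what the trial can say about safety. It does not affect the primary analysis.

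**What to change.** **Safety Analysis.** Add the risk difference, ciclesonide minus symptomatic treatment, in the proportion of patients with at least one adverse event, and likewise with at least one serious adverse event, each with a two-sided 95% confidence interval (for example Newcombe). Keep the chi-squared or Fisher p value as descriptive. State that the safety conclusion rests on the upper limit of the interval and that a non-significant test is not evidence of safety. No margin is required.

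**Abstract (Conclusions) and closing paragraph of the Discussion.** Replace the safety hypothesis to be found valid with a description of the excess adverse event rate that the interval excludes.

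**Cost.** A few sentences and two intervals from data already collected, with no additional patients. The downside is a weaker safety claim: even with equal observed rates of 5/45 or 9/45 in both arms, only excesses above about 14 to 17 points would be excluded.

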#### Interim Analysis

An intermediate analysis will be conducted after 50% participant enrollment has been achieved to determine whether the primary objective has been attained. If the trial treatment group shows significantly higher efficacy results than the standard treatment group (ie, efficacy suspension), or if the trial treatment group shows significantly lower efficacy results than the standard treatment group and drug superiority cannot be verified, even with the continuation of treatment (ie, inefficacy suspension), the independent monitoring committee will advise on the suspension of the study in order to prevent the continuation of treatment in the disadvantaged treatment group. In order to ensure an α error of 10% in the overall trial, the Lan and DeMets α spending function will be used to adjust for the redundancy of inspections in the intermediate and primary analyses, and the statistical significance of primary endpoint differences between groups will be studied. The O’Brien and Fleming-type α spending function will be used. A Bayesian predictive power based on a noninformative prior distribution will be used for inefficacy suspension determination in the proposed study.

#### Methods for Additional Analysis

Additional analyses will be conducted after the completion of the additional period and the finalization of the cases, from which data are obtained and presented in a statistical report for the representative physician.

#### Methods for Handling Missing Data

Questionable issues will be resolved after discussion between the representative physician and the statistical analysis manager. Missing values are not to be filled out, and details on the handling of outliers and abnormal values are to be regulated in the statistical analysis plan.

### Oversight and Monitoring

Quality control for ensuring compliance will be performed through monitoring by the Central Coordinating Unit of the Clinical Research Promotion Center at the Tokyo University Hospital. A monitoring plan has been created and approved by the representative physician and the authorizing clinical study examination committee. The principal physician who receives the monitoring reports is to notify the representative physician about the applicable report content as necessary.

No audit has been scheduled, and audits will only be conducted if serious problems are identified in the monitoring reports or if there are any events that impact patient safety.

All documents relating to the research are directly accessible for inspection.

### Composition of the Data Monitoring Committee

An independent Data and Safety Monitoring Board (DSMB) has been formed, and it consists of members with no financial or scientific conflicts of interest in this study. The DSMB chair is a clinician with extensive experience in respiratory medicine, DSMBs, and clinical research. The DSMB statistician is an experienced statistician. The other member of the DSMB is an experienced respiratory clinician. The committee’s remit is to protect the safety of trial participants by monitoring intermediate safety and operational data during trial implementation, and to provide suitable advice and suggestions to ensure the ethical and scientific validity of the study.

### Dissemination Plans

At 1 year after trial registration, the representative physician will report on the progress of this randomized controlled trial to the manager of the implementing medical institution and the Ministry of Health, Labor, and Welfare. A comprehensive report will be submitted at the end of the study.

Trial findings will be communicated at national and international scientific meetings by publications in a scientific journal. In addition, results will be disseminated to trial participants, study staff, clinicians, and patient groups via direct approaches and a variety of traditional and electronic media, including newsletters.

### Compensation Criteria

The principal physician, subphysician, and implementing medical institution must conduct suitable diagnoses and treatment and provide clinical care and other measures to ensure that the research subject is receiving the necessary care.

The representative physician has been enrolled in a clinical research insurance plan that includes compensation for the death or physical impediment of the research subject and medical expenses and care needed for the treatment of the health hazards in the research subject, in accordance with the payment conditions of clinical research insurance. The principal physician and subphysicians are also enrolled in a medical professional liability insurance plan.

## Results

The first trial participant was enrolled on April 3, 2020. Recruitment and registration are expected to be completed on September 30, 2020, while the follow-up of all participants is expected to be completed by October 31, 2020.

## Discussion

Preclinical data [12] have shown that ciclesonide can suppress the viral replication of coronaviruses in cell cultures [12,13], suggesting that ciclesonide can potentially be used to treat COVID-19. This multicenter, prospective, open-label randomized controlled trial has been designed to determine the efficacy and safety of ciclesonide in treating patients with asymptomatic and mild COVID-19. The rationale for choosing such patients was based on the findings of Iwabuchi et al [14,15], who indicated that the ideal ciclesonide administration period should be in the early intermediate stage of infection or the initial stage of pneumonia, prior to the worsening of symptoms.

The eligibility criteria in this study were designed to enroll study participants who had been diagnosed with SARS-CoV-2 infection without pneumonia and were not on any concomitant or prior medication that could affect the efficacy assessments. The trial processes of this study have been designed to be integrated within medical care at the participating hospitals, thereby enabling physicians to easily enroll participants without the need for a large research staff to compliment and implement the treatment, and learn more about the disease. Most of the clinical data will be routinely collected, except for SARS-CoV-2 antibody and viral genome quantification data. Trial staff have also been trained to adhere to the protocol.

There are some limitations that need to be considered. First, a placebo is not available because of the rights to the drug. Second, since this is an open-label study, there is potential for bias in the assessment. To avoid this, the primary endpoint analysis will be performed by a blinded independent radiologist. Third, ciclesonide is a steroid, and it is difficult to distinguish between its antiviral and anti-inflammatory effects.

Other trials that involve ciclesonide are in progress or in planning. Covis Pharma has launched a phase III clinical trial in the United States to evaluate the asthma drug, ciclesonide (ALVESCO), in treating nonhospitalized patients with symptomatic COVID-19 aged ≥12 years. In this US trial, participants will be given 320 µg of ciclesonide (ALVESCO) via metered-dose inhaler twice daily, along with standard supportive care or a placebo and standard supportive care. The primary endpoint of the Covis Pharma trial is the percentage of patients who were admitted to a hospital or died by day 30 [16]. The accumulation of findings from the RACCO study together with those from the other trials will be significant in developing interventions and treatments for COVID-19.

In conclusion, the RACCO study is an ongoing open-label randomized controlled trial that will provide the most definitive comparative effectiveness data to date and other important clinical outcomes data from the ciclesonide and symptomatic treatment groups. If the hypotheses that pneumonia exacerbation rate reduction is more significant in the ciclesonide treatment group than in the symptomatic treatment group and that ciclesonide is safe for use are valid, ciclesonide will provide an important therapeutic option for patients with COVID-19 that can be rapidly implemented in clinical practice.

## Abbreviations

CT: computed tomography
DSMB: Data and Safety Monitoring Board
EDC: electronic data capture
GCP: good clinical practice
jRCT: Japan Registry of Clinical Trials
MMRM: mixed model for repeated measures
PCR: polymerase chain reaction
RACCO: Randomized Ciclesonide COVID-19
REDCap: Research Electronic Data Capture
